## Abstract

**Background:**

Natural products may provide a source for the discovery and development of adjunctive pharmacological interventions to modulate the inflammatory pathways contributing to chronic disease. Xanthohumol, a flavonoid from the hops plant (*Humulus lupulus*), has antioxidant and anti-inflammatory properties and may act as a prebiotic to the intestinal microbiota. Xanthohumol is not currently approved as a drug by the US Food and Drug Administration (FDA), but is available as a dietary supplement and ingredient in medical foods. To formally test the safety of xanthohumol, a phase I clinical trial (“XMaS”) was designed and approved under an Investigational New Drug application to the US FDA. The main objective is to examine the clinical safety and subjective tolerability of xanthohumol in healthy adults compared to placebo. Additional aims are to monitor biomarkers related to inflammation, gut permeability, bile acid metabolism, routes, and in vivo products of xanthohumol metabolism, and to evaluate xanthohumol’s impact on gut microbial composition.

**Methods:**

The safety and tolerability of xanthohumol in healthy adults will be evaluated in a triple-masked, randomized, placebo-controlled trial. Participants will be randomized to either 24 mg/day of xanthohumol or placebo for 8 weeks. Blood cell counts, hepatic and renal function tests, electrolytes, and self-reported health-related quality of life measures will be collected every 2 weeks. Participants will be queried for adverse events throughout the trial. Xanthohumol metabolites in blood, urine, and stool will be measured. Biomarkers to be evaluated include plasma tumor necrosis factor-alpha, various interleukins, soluble CD14, lipopolysaccharide-binding protein, fecal calprotectin, and bile acids to assess impact on inflammatory and gut permeability-related mechanisms in vivo. Stool samples will be analyzed to determine effects on the gut microbiome.

**Discussion:**

This phase I clinical trial of xanthohumol will assess safety and tolerability in healthy adults, collect extensive biomarker data for assessment of potential mechanism(s), and provide comparison data necessary for future phase II trials in chronic disease(s). The design and robustness of the planned safety and mechanistic evaluations planned provide a model for drug discovery pursuits from natural products.

**Trial registration:**

ClinicalTrials.gov NCT03735420. Registered on November 8, 2018

## Introduction

### Background and rationale {6a}

Xanthohumol is a flavonoid constituent of the hops plant (*Humulus lupulus*), exerting antioxidant, anti-inflammatory, cancer chemopreventive, anti-hyperglycemic, and anti-hyperlipidemic activities [1–3]. Xanthohumol also acts as a prebiotic for intestinal microbiota and can alter the gut microbial composition in conjunction with its bacterial metabolites [4, 5]. Based on mechanisms of action supported by preclinical models, patients with numerous clinical conditions could potentially benefit from xanthohumol supplementation (Table 1). These effects come from known influences of xanthohumol on transcription factors that may provide upstream effects on inflammatory processes [6]. For instance, transcription factors that regulate gene expression known to be involved in the pathogenesis and progression of a broad array of human diseases are modulated by xanthohumol, including nuclear factor-kappa B (NFκB) [7–10], nuclear factor erythroid 2-related factor 2 (NRF2) [11, 12], and the farnesoid X receptor (FXR) [13, 14] (see Table 1).

**Table 1 Tab1:** Biologic mechanisms of xanthohumol on transcription factors and pertinent clinical conditions

Transcription factor	Xanthohumol mechanisms	Pertinent clinical conditions
Farnesoid X receptor (FXR)	FXR agonist in vitro and in vivo	• Type 2 diabetes mellitus • Metabolic syndrome • Dyslipidemia • Obesity • Non-alcoholic fatty liver disease • Non-alcoholic steato-hepatitis • Cholelithiasis • Inflammatory bowel disease • Cancer
Nuclear factor-kappa B (NFkB)	Inhibits activation of NFkB in vitro and in vivo	• Inflammatory bowel disease • Rheumatic disease • Asthma • Autoimmunity • Cancer
Nuclear factor erythroid 2-related factor 2 (NRF2)	Increases expression of and activation of NRF2 in vitro	• Autoimmunity • Alzheimer’s disease • Inflammatory bowel disease • Cancer

Using in vitro binding studies and in silico models, xanthohumol and its metabolites are ligands for the FXR and preliminary in vitro data indicates xanthohumol activates FXR-regulated genes at low concentrations, supporting xanthohumol functions as a pharmacologic agonist of FXR [4, 13]. The FXR receptor is known to regulate intestinal permeability as well as innate immunity including production of the pro-inflammatory cytokines: interleukin (IL)-1β, IL-6, IL-8, IL-10, IL-12p70, tumor necrosis factor alpha (TNF-α), and interferon-gamma (IFN-γ) [15, 16]. FXR agonists have been tested in animal models and early clinical trials, showing promise for altering inflammatory signaling pathways [15, 17]. Thus, xanthohumol has the potential to be a novel therapeutic in pertinent diseases (e.g., inflammatory bowel disease) by acting as an FXR agonist, reducing inflammation, modulating bile acid metabolism, and reducing gut permeability. However, xanthohumol is not currently approved as drug by the FDA for the treatment, cure, prevention, or mitigation of disease, despite being available as a dietary supplement in both crude and standardized extracts from hops.

For a segment of the population, xanthohumol is commonly consumed in the diet through beer, which contains 0.5–4 mg/L depending on brewing processes [18]. Thus, xanthohumol appears safe when administered orally in amounts commonly contained in the diet through beer. Furthermore, both hops and hops oil are considered Generally Recognized as Safe in the USA [19]. Animal models have shown body morphological changes, including decreased weight in some models, without effect on reproduction or histopathological changes in the bone marrow, liver, exocrine pancreas, kidneys, muscle, thyroid, ovaries, and testes or changes in complete blood counts in doses up to 1000 mg/kg of body weight [20–22]. Although xanthohumol has been formally evaluated in a pharmacokinetics study in humans, no previous studies have prospectively evaluated the safety and tolerability of xanthohumol, as an isolated constituent, in human subjects [23].

In the planned phase I XMaS trial, healthy participants will be recruited and randomized to either 24 mg of xanthohumol in a rice protein vehicle or rice protein placebo for 8 weeks. Routine clinical biomarkers and quality of life of the participants will be evaluated in 2-week intervals to examine the safety and tolerability of oral supplementation with xanthohumol. Additional aims are to collect data on biomarkers related to inflammation, gut permeability, bile acid metabolism, routes of xanthohumol metabolism, and potential impacts on gut microbiota.

## Methods/design

### Objectives {7}

The primary aim of this trial is to determine the safety and tolerability of xanthohumol in healthy adults through administration of 24 mg/day of xanthohumol, compared to placebo. This aim will be met by assessing routine clinical toxicology measures compared to baseline values, including complete blood count, electrolytes, estimated glomerular filtration rate, blood urea nitrogen to creatinine ratio, aspartate aminotransferase (AST), alanine aminotransferase (ALT), ɣ-glutamyl transferase (GGT), alkaline phosphatase, and bilirubin, plus self-reported adverse events. The secondary aim is to measure effects of xanthohumol on TNF-α as a biomarker of active inflammation [14, 16, 24, 25]. The tertiary aim is to collect preliminary data related to effects on gut permeability, xanthohumol metabolism, and impact on the gut microbiome for a subsequent phase II trial in adults with Crohn’s disease based on mechanisms described in Table 1. Tertiary outcome measures include xanthohumol metabolites in the blood and urine; biomarkers of gut permeability, enterocyte inflammation, and systemic immune activity; assessment of bile acid metabolism; gut microbial composition; and identification of gut microbial proteins targeted by xanthohumol. Specific biomarker information by aim can be found in Table 2. Summary safety data will be reported upon trial completion as the frequency of new-onset laboratory abnormalities, including changes in anemia status, liver function tests (AST, ALT, GGT, bilirubin, and alkaline phosphatase), electrolytes, and/or creatinine and estimated glomerular filtration rate (eGFR).

**Table 2 Tab2:** Aims and methods of assessment

Aim	Marker	Assessment method
1. *Safety & Tolerability*	a. RBC, WBC, platelets b. eGFR, electrolytes, BUN:Cr, AST, ALT, GGT, alkaline phosphatase, bilirubin c. Adverse events, quality of life	a. Complete Blood Count (CBC) b. Comprehensive Metabolic Panel (CMP) c. Adverse Events Questionnaire, PROMIS-29
2. *Inflammation*	a. Inflammatory cytokines: IL-1β, IL-2, IL-6, IL-8, IL-10, TNF-α, and IL-12p70 b. Fecal calprotectin	a. Serum or plasma analysis b. Stool analysis
3a. *Gut Permeability*	a. CD14, lipopolysaccharide binding protein, intestinal fatty acid binding protein	a. Plasma analysis
3b. *Xanthohumol Metabolism*	a. Xanthohumol metabolite profiles	a. 24-hour urinalysis, plasma analysis, stool analysis
3c. *Microbial Composition Changes*	a. Metagenomic DNA sequencing and taxonomic profiling b. Proteomic characterization	a. Compared to xanthohumol metabolite profiles b. Activity-based proteomic assay

## Hypotheses

We hypothesize that xanthohumol, at a dosage of 24 mg per day, will be safe and tolerable in trial participants as demonstrated by frequency of laboratory abnormalities or reported adverse events observed between groups not being significantly higher, and at most 50% higher in the intervention group. Additionally, we hypothesize xanthohumol and its microbiota-derived metabolites will reduce biomarkers of inflammation and modify barrier function in the inflamed gut. We anticipate xanthohumol will produce a specific microbiota-based biological mechanistic signature, which will provide the groundwork to determine its therapeutic potential in various chronic diseases.

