### Sample size {14}

A sample size of twenty-four (*n* = 12 per group) provides 80% power to detect a 50% difference in proportions of participants between groups by chi-squared test experiencing a laboratory abnormality or adverse event at a significance threshold of *α* = 0.05. To account for up to 25% attrition, up to 16 adults (8 biologically male and 8 biologically female participants) will be enrolled in each study arm. Given that this phase I trial is intended as a step toward a phase II clinical trial in Crohn’s disease, for which few effective treatments exist, the investigational drug is commonly available in the diet, and previous human studies have not suggested any toxicity, the present trial was powered to detect gross toxicity resulting in frequent adverse events and/or laboratory-measurable toxicity. However, interim halting criteria were also used to assess safety; an accumulated frequency of 25% reaching laboratory halting criteria was pre-specified as a criterion for halting the trial and requiring detailed review by the FDA, NCCIH, and IRB.

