As an element of the evaluation for safety of the intervention, the percentage of laboratory newly abnormal (for values that were within the clinically normal range at baseline) per clinical laboratory reference ranges for each lab parameter will be reported at each time point and the percentage will be compared between groups by Fisher’s exact test. Assessment for changes in the distribution of each lab parameter will be performed by presenting means and confidence intervals (CI) for the change in each group, as well as the mean CI for the difference between groups; significance will be tested using 2-sided, unpaired *t* tests (or, if inspection of distributions indicates strong non-normality, with a non-parametric Wilcoxon signed rank test) of the mean values for the xanthohumol group compared to the placebo group. Assessment for overall *increases* or *decreases* in collected parameters will be tested for linear trends of the means by linear mixed ANOVA, considered significant if *p* < 0.05, with time point as a repeated factor. This may be suggestive of evidence for cumulative toxicity if trending in a clinically deleterious direction.

Health-related quality of life, measured by PROMIS-29, is included as a tertiary measure of gross changes in health. PROMIS-29 includes 7 validated subscales (physical function, anxiety, depression, pain intensity, pain interference, sleep, social interactions), each of which will be calculated as a mean by group, and means will be compared between xanthohumol and placebo, with the primary comparison being of mean changes from baseline to week 8. Significance of changes in QOL measures will be tested according to the same plan outlined for laboratory markers, above.

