## Discussion

The main objective of the phase I XMaS trial is to examine the safety and tolerability of daily xanthohumol administration in healthy adults over an 8-week time frame. This objective will be accomplished by monitoring routine clinical laboratory parameters, assessing quality of life, and administering standardized adverse event queries throughout the study and using these data to make a composite assessment of clinical safety, with input from the FDA and NCCIH. Tolerability of xanthohumol will be assessed by monitoring the number and proportion of participants who discontinue the intervention citing adverse effects, changes in the seven health-related quality of life domains captured via the PROMIS-29 questionnaire, and the severity and duration of symptoms, for comparison between treatment and control groups.

Preclinical studies have demonstrated that xanthohumol has multiple therapeutic properties including modulating inflammatory pathways by acting as an FXR agonist and via inhibition of NFκB activation, regulation of gut permeability and bile acid metabolism by acting as an FXR modulator, and regulation of antioxidant protein expression via activation of NRF2 [7–13, 15, 51]. By regulating these transcription factors, xanthohumol may impact expression of numerous downstream genes in vivo and therefore has therapeutic promise for multiple disease states, including Crohn’s disease (Table 1). Furthermore, xanthohumol acts as a prebiotic for intestinal microbiota and, along with its bacterial metabolites, alters the gut microbiota [5]. Therefore, additional aims of the phase I XMaS trial are to collect data on biomarkers related to inflammation, gut permeability, bile acid metabolism, xanthohumol metabolism, and the impact of xanthohumol on gut microbiota to assess if these mechanisms are modified in vivo.

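### Safety is to be demonstrated by a non-significant difference and an observed excess of at most 50%, with no confidence limit on the difference in event proportions

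*Protocol article*

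**What the plan says.** The Hypotheses section states that the product "will be safe and tolerable in trial participants as demonstrated by frequency" of laboratory abnormalities or adverse events meeting two conditions: "frequency of laboratory abnormalities or reported adverse events observed between groups not being significantly higher, and at most 50% higher in the intervention group". It does not say whether 50% is a ratio or a number of percentage points.

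Sample size {14} plans 12 evaluable participants per arm, up to 16 enrolled, and claims "80% power to detect a 50% difference in proportions of participants between groups by chi-squared test" at alpha 0.05. It adds that the trial is powered for gross toxicity. It gives no placebo event rate.

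In the statistical methods section, newly abnormal laboratory values are tabulated for each parameter at each time point, and "the percentage will be compared between groups by" Fisher's exact test. The confidence intervals in the same paragraph are for mean changes in laboratory values. The adverse event section {22} promises a comparison of frequency between groups and no interval. The Discussion speaks of "using these data to make a composite assessment of clinical safety", with input from two outside bodies.

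**The concern.** Failure to find a significant excess is weak evidence of no excess when the trial is small. The smaller and noisier the trial, the easier the first condition is to meet. The second condition compares observed frequencies and ignores their uncertainty. Together they set the stated standard for the primary aim without saying how large a true excess the data would rule out. At stake is how far the result can be relied on in planning the phase II trial in Crohn's disease that this study is meant to precede.

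**Working it through.** **Inputs.** 12 per arm, alpha 0.05, chi-squared for the participant-level comparison (Sample size {14}); Fisher for new laboratory abnormalities (statistical methods). Tests are taken as two-sided, because sidedness for proportions is not stated. All placebo rates are assumptions.

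**The plan's own figure.** Power = Φ{[Δ√n − 1.96√(2p̄(1−p̄))] / √(p0(1−p0) + p1(1−p1))}. For 5% v 55%, Δ = 0.50, p̄ = 0.30, n = 12: (1.732 − 1.96 × 0.648) / √(0.0475 + 0.2475) = 0.462 / 0.543 = 0.85, and Φ(0.85) = 0.80. So 80% reproduces for a 50-point difference (0.71–0.86 over placebo rates of 0–50%). Read as a 1.5-fold ratio it does not: power is 0.06–0.39 for placebo rates of 10–60%.

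**Pass probability.** Let X and Y be the numbers of placebo and xanthohumol participants with an event. P(pass) = Σ b(x; 12, p0) · b(y; 12, p1) over all 13 × 13 outcomes that meet the rule.
- Ratio reading: not significantly higher and Y ≤ 1.5X.
- Point reading: not significantly higher and Y − X ≤ 6.
- For comparison: one-sided 95% Newcombe upper limit for the difference below 50 points.

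No 12 v 12 outcome is non-significant with an excess above 6, under either test. On the point reading the rule is therefore the significance condition alone, and one column serves for both.

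| True rates, placebo v xanthohumol | Not significant = point reading passes (Fisher / chi-squared) | Ratio reading passes | Upper limit < 50 points |
|---|---|---|---|
| 10% v 30% | 90% / 80% | 24% | 68% |
| 20% v 40% | 91% / 82% | 35% | 57% |
| 5% v 55% | 31% / 17% | 0.7% | 7.4% |
| 10% v 60% | 36% / 21% | 1.8% | 6.2% |
| 20% v 70% | 39% / 23% | 4.8% | 5.5% |
| 5% in both | >99.9% / 99.9% | 71% | 99.9% |
| 10% in both | 99.9% / 99.3% | 66% | 99.0% |
| 20% in both | 99.4% / 98.1% | 71% | 94.5% |
| 30% in both | 99.1% / 97.5% | 76% | 88.8% |
| 50% in both | 98.9% / 96.8% | 85% | 84.7% |

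In the ratio column the choice of test makes no visible difference at these rates.

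**Single outcomes.** Against 0/12 on placebo, Fisher needs 5/12 on xanthohumol (p = 0.037); 4/12 gives p = 0.093. On the ratio reading 0/12 v 1/12 already fails. A passing result of 4/12 v 6/12 has ratio 1.5 with standard error of the log ratio √(1/6 − 1/12 + 1/4 − 1/12) = 0.5, so the 95% interval is 0.56 to 4.0. The difference is 17 points (95% Newcombe −20 to +48). With 9 or more of 12 placebo participants affected, no xanthohumol result can fail either condition.

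**At 16 per arm (Fisher).** 20% v 40% passes 33% (ratio) or 87% (points). An inert product at 10% fails 33% on the ratio reading.

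**The case against.** The sentence is a hypothesis, not an analysis rule. The statistical methods section names the mean change from baseline to week 8 as the primary outcome metric and gives it confidence intervals. Sample size {14} says openly that only gross toxicity is in view, there are halting criteria, and the Discussion describes a composite assessment. This stands in part: a reader might infer that this sentence alone decides whether the product is declared safe, and the documents do not support that. None of these passages changes the evidential standard the sentence sets, though, and none puts an interval on event proportions.

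A reader might also infer that the rule both lets gross toxicity through and often fails an inert product. That mixes two readings. An inert product fails often only on the ratio reading; on the point reading it fails about 1% or less (Fisher) or at most about 3% (chi-squared). A true 50-point excess passes 31–39% only on the point reading with Fisher. The participant-level comparison was sized with chi-squared, which gives 17–23%, and on the ratio reading the figure is 0.7–4.8% for the pairs shown.

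The rates are assumed. An 81-item questionnaire at each visit makes a high any-event rate plausible, and at 70% in both arms an inert product passes the ratio reading about 94% of the time.

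Finally, a 50-point upper-limit rule is not uniformly stricter: it passes 10% v 30% and 20% v 40% more often than the ratio reading does (68% and 57%, against 24% and 35%). That is why it cannot simply be substituted as a test of safety.

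**Conclusion.** The concern holds in this form: the Hypotheses section uses a non-significant difference and a capped observed excess to demonstrate safety, and the article puts no confidence limit on event proportions. Whichever way 50% is read, a trial of this size will often satisfy the rule when events are truly doubled: 35% of the time (ratio) or 82–91% (points) at 20% v 40%. The harm to an inert product, 24–34% failing at placebo rates of 5–30%, belongs to the ratio reading only. The sizes rest on assumed placebo rates, two-sided tests and 12 evaluable per arm; the pattern is the same at 16. The stated 80% power is not itself in error, since it reproduces for about 5% v 55%. Severity: should fix.

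**What to change.** 1. In the Hypotheses section, remove non-significance as the demonstration of safety, and say whether 50% is a ratio or percentage points.
2. Report the between-group difference in the proportion of participants with at least one new-onset laboratory abnormality or adverse event, with an exact or Newcombe confidence interval. Give such an interval beside each frequency comparison in the statistical methods and adverse event sections.
3. Limit the conclusion to the size of excess that the upper limit excludes.
4. If a 50-point upper-limit criterion is kept, because that is the effect for which the 80% power reproduces, state that it supports only the claim that an excess of 50 percentage points is excluded, not that the product is safe. Give its properties: a true 50-point excess passes about 6–7% of the time and an inert product 85–99.9% (rates of 5–50%), but 10% v 30% still passes in 68% and 20% v 40% in 57% of trials.

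The cost is wording and a few added intervals, with no extra participants. The downside is a weaker permitted claim.

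### The Hypotheses section lets non-significance and an uninterrupted point-estimate limit demonstrate safety, with no interval and an unreconciled 50% scale

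*Protocol article*

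**What the plan says.** The Hypotheses section predicts that the product, at the trial dose, "will be safe and tolerable in trial participants as demonstrated by frequency of laboratory abnormalities or reported adverse events". The requirement it then sets for those frequencies has two parts: "observed between groups not being significantly higher, and at most 50% higher in the intervention group". The parts are joined by 'and', and neither carries a confidence limit or a non-inferiority test.

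Sample size {14} starts from "A sample size of twenty-four", that is 12 in each arm, and claims that this number "provides 80% power to detect a 50% difference in proportions of participants between groups by chi-squared test". The outcome compared is having any abnormal laboratory result or any adverse event, and the test is made "at a significance threshold of *α* = 0.05". The same section adds that "the present trial was powered to detect gross toxicity resulting in frequent adverse events and/or laboratory-measurable toxicity".

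The statistical methods section says that, for newly abnormal laboratory values, "the percentage will be compared between groups by Fisher’s exact test", separately for each parameter and time point. The confidence intervals planned there are for changes in the laboratory values, not for differences in event frequency.

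**The concern.** The first condition counts failure to find a difference as evidence of safety. In an arm of 12, only a very large excess is likely to reach significance, so the condition is easily met whether or not the product is harmful.

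The second condition limits the observed frequency alone. It makes no allowance for sampling error, which is large at this size.

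The two uses of 50% also differ. In the Hypotheses, 50% higher reads naturally as a ratio of 1.5. In Sample size {14}, a 50% difference in proportions reads as 50 percentage points. The rule behaves very differently under the two readings.

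The trial is meant to lead to a phase II trial in Crohn's disease, a population the methods section describes as potentially vulnerable to the toxicities being measured. A safety statement resting on this rule would not tell the reader how large an excess the data rule out.

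**Working it through.** **Inputs.** 12 evaluable per arm, chi-squared test, 80% power, α = 0.05 (Sample size {14}); Fisher's exact test (statistical methods); the two-part rule (Hypotheses). Sidedness of the proportion test is not stated, so two-sided is assumed. No placebo event rate is given, so it is varied.

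**1. The plan's own figure.** Normal approximation without continuity correction:

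power = Φ{ [ |p₂ − p₁|√n − 1.96√(2p̄(1 − p̄)) ] / √[p₁(1 − p₁) + p₂(1 − p₂)] }

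For 5% v 55%, n = 12, p̄ = 0.30: (0.50 × 3.464 − 1.96 × 0.648) / 0.543 = 0.85, so power is 80.2%. The figure reproduces as a 50-point difference at a placebo rate near 5%. It is 76% for 10% v 60% and 71% for 25% v 75%.

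Read as a relative 50% increase, power at 12 per arm is 5.5% (10% v 15%), 8% (20% v 30%), 11% (30% v 45%), 16% (40% v 60%) and 24% (50% v 75%). The sample-size text therefore works only in percentage points.

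**2. Full rule, relative reading.** Let a and b be the numbers with an event on xanthohumol and placebo. The rule passes if the excess is not significant (p ≥ 0.05) and a ≤ 1.5b.

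P(pass) = Σ Bin(a; 12, p_X) × Bin(b; 12, p_P) over all passing (a, b)

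Hand check for a harmless product at 10% in both arms; the rule fails when:
- b = 0 and a ≥ 1: 0.282 × 0.718 = 0.203
- b = 1 and a ≥ 2: 0.377 × 0.341 = 0.128
- b = 2 and a ≥ 4: 0.230 × 0.026 = 0.006

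The sum is 0.337, or 34%; larger b adds almost nothing.

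| True rates, placebo to xanthohumol | Rule passes |
|---|---|
| 10% to 20% | 41% |
| 20% to 40% | 35% |
| 25% to 50% | 32% |
| 30% to 60% | 29% |

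| Equal true rate | Harmless product fails |
|---|---|
| 10% | 34% |
| 20% | 29% |
| 30% | 24% |
| 50% | 15% |
| 70% | 6.3% (Fisher), 6.6% (chi-squared) |

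Except in the last row, both tests give the same figures. With all 16 enrolled per arm evaluable, little changes: 25% to 50% passes in 29%, and a harmless product fails in 33% at 10% and 12% at 50%.

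**3. Full rule, percentage-point reading.** At 12 per arm the largest non-significant observed excess is 4 participants (chi-squared) or 5 (Fisher). A 50-point excess is 6, so it is always significant already. The limit never binds, and the rule reduces to non-significance. A rise from 25% to 50% passes in 74% (chi-squared) or 86% (Fisher), and 20% to 40% in 82% or 91%. A harmless product fails in about 0% to 3%.

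**4. What an interval would show.** With 0 events in 12, the two-sided exact 95% upper limit for that arm is 1 − 0.025^(1/12) = 26.5%.

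**The case against.** The best defence is that the sentence is a hypothesis and not the whole safety decision. The primary outcome metric is mean laboratory change to week 8, with intervals for the between-group difference. The document openly limits its power to gross toxicity, sets withdrawal and halting criteria, has a data safety monitoring board, and in the Discussion describes a composite assessment with FDA and NCCIH input. This stands as a reason to rate the point below a must-fix. It does not repair the sentence: none of these provisions replaces or qualifies what is said to demonstrate safety, and none puts an interval on event frequencies.

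Some stronger inferences are tempting but unsupported:

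- That a rise from 0% to 50% would be tolerated on the point reading. It would not: 6/12 v 0/12 gives p = 0.005 (chi-squared) and 0.014 (Fisher), so the significance condition fails.
- That 4/12 v 0/12 shows the rule passing harm. It is non-significant by Fisher (p = 0.093) but significant by the chi-squared test named in Sample size {14} (p = 0.028), and it breaches the relative limit in any case.
- That the rule can be judged on its significance condition alone. On the relative reading the second condition matters a great deal: true rates of 0% v 33% pass the full rule in only 0.8% of trials, and 10% v 40% in 12%.
- That frequent passing of harm and frequent failing of a harmless product hold on every reading. The second problem arises only on the relative reading, and it shrinks as event rates rise. High rates are plausible with an 81-item questionnaire at every visit.
- That the sample size is miscalculated. It reproduces under the conditions in step 1.

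**Conclusion.** The rule is wrong as written. It equates non-significance at 12 per arm with demonstrated safety, limits a point estimate without an interval, and uses 50% on a scale that does not match the sample-size section.

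On the relative reading it passes true doublings about three to four times in ten, and it fails a harmless product in about 6% to 34% of trials across equal rates of 70% down to 10%. On the percentage-point reading it is a non-significance rule only: it misses a 25% to 50% doubling in about three-quarters or more of trials but seldom fails a harmless product.

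These figures rest on assumed placebo rates, independent binomial counts, 12 evaluable per arm and two-sided testing at 0.05. The point is a should-fix, because the other safeguards mean that the safety judgement need not rest on this sentence alone.

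**What to change.** 1. In the Hypotheses, delete the wording that makes a non-significant excess the demonstration of safety.
2. Report the risk difference, xanthohumol minus placebo, in participants with at least one new laboratory abnormality or adverse event, with a two-sided 95% confidence interval (Newcombe or exact).
3. Word the conclusion by the upper limit: an excess above X percentage points is excluded.
4. If a 50% limit is kept, state it once, on a scale consistent with Sample size {14}, and apply it to that upper limit.

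The scale matters. Excluding a 50% relative excess when true rates are equal (one-sided α 0.025, 80% power) would need about 566, 252, 147, 95 or 63 per arm at placebo rates of 10%, 20%, 30%, 40% or 50%, which is out of reach here. A 50-point limit needs about 11, 14 or 16 per arm at 20%, 30% or 50%, close to the planned size. Whether so wide a limit is informative is for the sponsor to justify.

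The cost is a few sentences and one interval per event table. The sample size does not change. The safety conclusion becomes more modest.
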